# Evaluation of clinical efficacy of silver-needle warm acupuncture in treating adults with acute low back pain due to lumbosacral disc herniation: study protocol for a randomized controlled trial

**DOI:** 10.1186/s13063-019-3566-2

**Published:** 2019-07-31

**Keywords:** Acupuncture therapy, Low back pain, Intervertebral disc degeneration, Radiculopathy

## Abstract

**Background:**

As a common cause of low back pain, lumbosacral disc herniation (LDH) is usually dealt with using non-surgical interventions. In the face of concerns about prescription opioid abuse, alternative and complementary treatments may be promising, among which silver-needle warm acupuncture is considered as an upgrading option for its potential anti-inflammatory and strong analgesic effect for patients with chronic pain. In this proposed study, we aim to assess its clinical efficacy in comparison with conventional stainless steel filiform-needle warm acupuncture.

**Methods/design:**

This is a randomized, two-armed, patient- and assessor-blinded trial. One hundred and sixty eligible patients recruited from December 2018 to June 2020 in three centers will be assigned for warm acupuncture treatment with either stainless steel filiform or silver needles. Nine sessions of 20-min treatment will be conducted during 3 consecutive weeks. Assessments with instruments including the Oswestry Disability Index, the visual analog scale, and the Japanese Orthopedic Association Back Pain Evaluation Questionnaire will be performed at four time points to explore the difference of clinical efficacy between two groups.

**Discussion:**

If the results show that participants treated with silver-needle warm acupuncture gain a greater improvement in terms of pain intensity, physical function, and quality of life, this study is expected to offer reliable evidence to widely push this treatment for LDH in clinical practice.

**Trial registration:**

Chinese Clinical Trial Registry, ChiCTR1800019051. Registered on 24 October 2018.

**Electronic supplementary material:**

The online version of this article (10.1186/s13063-019-3566-2) contains supplementary material, which is available to authorized users.

## Background and rationale

Lumbosacral disc herniation (LDH), usually referred as lumbosacral radiculopathy (LR) in Western countries [1], is one of the most commonly seen degenerative spinal disorders, accounting for 85% of low back pain with (or without) sciatica [2]. According to the “Chinese Consensus on Rehabilitation of Lumbar Disc Herniation,” first published in 2017, only 10–20% of LDH which might lead to severe neurologic deficits requires surgical intervention [3], indicating that the majority of patients with low back pain due to LDH can obtain symptomatic relief, though not a radical cure, simply through conservative therapies. However, the overuse of prescription opioids for analgesic purposes has turned out to be a great challenge characterized by substantial health care and societal costs [4]. Thus, public attention is gradually shifting to complementary and alternative medicine (CAM).

Among these alternatives under the CAM category, warm acupuncture, a combination of acupuncture therapy and thermal therapy (with a heat source like burning herbal moxa, laser light, or a multi-functional moxibustion apparatus), is often considered as an ideal option for patients who fail to benefit from manual or electrical acupuncture therapy. It is assumed that the steady and in-depth thermal conduction introduced by the inserted needle will exert a potent anti-inflammatory effect at the local lesions, leading to a strong analgesic effect [5].

Compared to the conventional stainless steel filiform type, needles made of precious metals (such as silver and gold) have been proven to have a better thermal effect in a warm acupuncture procedure, due to their higher thermal conductivity. The existing literature [6] suggests that, for a burning herbal moxa warm acupuncture procedure, a silver needle surpasses a stainless steel filiform needle, with a temperature of approximately 50 °C at the intradermal layer and approximately 40 °C at the tip. This temperature range is high enough to produce a positive effect on microcirculation at the local lesions without producing any discomfort or burns [7].

Taking the public concerns of opioid abuse and the favorable safety profile of acupuncture treatment into consideration, we have used the findings and experience from decades of clinical practice to design this randomized controlled trial (RCT), with the purpose of collecting reliable evidence for applying silver-needle warm acupuncture to low back pain caused by LDH.

### Objectives and hypothesis

In this RCT we intend to assess the clinical efficacy of silver-needle warm acupuncture versus stainless steel filiform-needle warm acupuncture on low back pain due to LDH by comparing the change of the Oswestry Disability Index (ODI), the visual analog scale (VAS), and the lumbar spine dysfunction score of the Japanese Orthopedic Association Back Pain Evaluation Questionnaire (JOABPEQ). We also expect to prove that silver-needle warm acupuncture can be an ideal conservative alternative for patients with acute low back pain who fail in conventional acupuncture therapy. Our hypothesis is that participants treated with silver-needle warm acupuncture will receive better improvement in severity of pain, physical function, and quality of life, both short and long term.

## Methods

### Study design and setting

Developed according to the Standard Protocol Items: Recommendations for Interventional Trials (SPIRIT) Statement [8] (the SPIRIT checklist is shown in Additional file 1), this trial will be a randomized, two parallel-armed, patient- and assessor-blinded study conducted in three centers (Shanghai Pudong Hospital of Traditional Chinese Medicine (TCM), Longhua Hospital affiliated to Shanghai University of TCM, and Baoshan Hospital of Integrated Traditional Chinese and Western Medicine) in Shanghai from December 2018 to November 2021. Research results will be reported consistent with Consolidated Standards of Reporting Trials (CONSORT) guidelines [9] and the Revised Standards for Reporting Interventions in Clinical Trials of Acupuncture (STRICTA) [10]. A flowchart of this trial procedure is shown in Fig. 1. This RCT has been approved by the Ethics Committee of Shanghai Pudong Hospital of TCM on 11 October 2018, meaning all interested participants will sign a written informed consent form (see Additional file 4) with a clear understanding of the purpose, study procedure, and all potential risks of this trial. All written informed consent forms will be collected and obtained by the chief coordinator.

**Fig. 1 Fig1:**
[figure not shown]
Study process: flowchart of study procedure

### Participant recruitment

Recruitment methods applied in this study include advertising through (1) social media (the official homepage or WeChat platform of Shanghai Pudong Hospital of TCM), (2) bulletin boards, and (3) flyers at affiliated community health service centers. Any potential participants can contact our researchers by our provided phone number and make an appointment for their screening visit. After potential participants have received a detailed explanation about the study protocol, only those who fully meet the selection criteria and sign the written informed consent form will be enrolled and randomly allocated to receive either silver-needle or stainless steel filiform-needle warm acupuncture treatment. The enrollment of participants was anticipated to start in December 2018 and end in June 2020.

### Sample size

The sample size calculation is conducted based on the result of a conventional therapy RCT [11], in which the post-treatment ODI score ($$ \overline{x} $$ ± S) decreased to 26.29 ± 18.02 in the intervention group, and 34.58 ± 15.10 in the control group. It is indicated that, in the condition of α = 0.05 (two-sided) and 1 – β = 80%, the sample size of our proposed study should be 128 (64 for each group). Allowing for a sample loss of 20%, the final sample size is inflated to 160 in total with a 1:1 allocation ratio.

### Selection criteria

#### Inclusion criteria

We intend to include patients aged 20–60 who:Have two of the following symptoms and signs confirmed by orthopedists of each center: (a) low back pain with or without lower extremity pain, lasting no more than 12 weeks and exacerbating with increased abdominal pressure; (b) scoliosis, paravertebral tenderness; (c) limited range of forward bending and a positive Lasegue’ s sign or Mackiewicz’ s sign; (d) paresthesia, dysreflexia, myodynamia, or even muscle atrophy in a lower extremityHave imaging evidence (X-ray, computed tomography, or magnetic resonance imaging scan) supporting a confirmed diagnosis of LDH.Indicate a VAS ≥ 5 on the first visitMeet the criteria for the Cold-Dampness-Bi syndrome based on TCM theory determined by medical history review and examination [12] (cardinal symptoms such as recurrent ache, heaviness, or soreness in the lower back, cold limbs, restricted lumbar function; physical examination symptoms such as pale tongue with white or thick coating, sunken and tight pulse).

In the inclusion criteria, we emphasize the use of TCM diagnoses based on symptom differentiation for the following reasons. According to the theory of TCM, the Cold-Dampness syndrome is most commonly detected in patients with low back pain due to LDH. In this scenario, warm acupuncture is especially suitable for a Cold-Dampness syndrome pattern due to its function of dispelling cold, removing dampness, and warming and activating meridians. Also, acupuncturists should always tailor an acupoint prescription to be consistent with a patient’s real condition so that a better therapeutic effect can be achieved. However, this can be the source of performance bias. Thus, we want to target a community who can share a relatively standardized treatment protocol to ensure that the research finding is both rigorous and applicable.

#### Exclusion criteria

Participants will be excluded if they:Suffer from cauda equina nerve damage, manifested as saddle anesthesia, bladder and bowel dysfunction, or sexual dysfunction; or suffer from LDH complicated by sciatica of the nerve trunk, piriformis syndrome, or other spinal diseases such as lumbar spinal stenosis, lumbar spondylolisthesis, ankylosing spondylitis, or spinal tuberculosisAppear to have a life-threatening complication or contraindication to acupuncture therapy such as heart disease, liver or kidney dysfunction, poorly controlled diabetes mellitus, or coagulation dysfunctionAre pregnant or lactating womenHave had other therapy or treatment related to LDH (including kinesitherapy, manipulative therapy, traction therapy, physical therapy, pharmacotherapy such as non-steroidal anti-inflammatory drugs [NSAIDs], epidural injection of corticosteroids or anesthetics, or surgical therapy) in the past 3 months.

#### Treatment rationale

Although acupuncture-related treatments, such as manual acupuncture, warm acupuncture, or electroacupuncture, have been applied for low back pain due to LDH for decades, and there are thousands of relevant clinical study reports, the most appropriate acupoint regimen has not yet been determined. In order to ensure that the study protocol is as rigorous as possible, we adopted the result of a literature review [13] and selected the most commonly used eight points (bilateral BL23, BL25, and BL54 and unilateral EX-B2 15/16 of the affected side; see Additional file 2) for low back pain due to LDH with Cold-Dampness syndrome as the core acupoints of a pragmatic regimen. This regimen allows the acupuncturist to add no more than a pair of other points based on the individualized tenderness, symptoms, or signs of each participant.

#### Treatment regimen

All participants will receive three sessions of 20-min treatment each week for 3 consecutive weeks, amounting to nine sessions in total.

The indoor temperature will be maintained at 25 °C by using a central air conditioner during treatment to minimize the influence of natural convection. In each session, the participant will be required to rest for 10 min in the treatment room before assuming a prone position.

After sterilizing the skin of selected points with alcohol pads (concentration of 75%), acupuncturists will insert the needles (0.40 mm * 75 mm) vertically to a depth of 30–50 mm and manipulate manually until the needle sensation (*Deqi*) is obtained. Needles on the eight core acupoints will be wrapped and fixed by the specially designed heat pipe, i.e., a tiny copper tube (2 mm * 0.5 mm * 20 mm) with a heatproof cork bottom, which will fit closely to the ceramic heat probe of a 15-output-set Multi-Function Moxibustion Apparatus (DAJ-23, XiangHe Chinese Traditional Medicine Instruments Co., Ltd., Heilongjiang, China; see Additional file 3). The output temperature of the device will be set in advance at 55 °C, implying that, after being attached to the ceramic heat probe for 2–3 min, the temperature at the intradermal part of the inserted needle will be stable and not exceed 50 °C. Twenty minutes later, acupuncturists will remove the ceramic heat probes, heat pipes, and needles cautiously and check thoroughly for any possible blisters or bleeding. During the trial, participants will be recommended to get more rest and avoid lifting of heavy loads or lumbar exertion (functional rehabilitation training like hip bridges, sit-ups, pull-ups, etc.) in their daily life.

The only difference between the two groups lies in the material of the needles. For the intervention group, we adopt the reusable, thin silver needles with a silver purity of 70 % (Hwato Medical Material Co., Ltd., Suzhou, China). To avoid contamination and cross-infection, every used silver needle will be strictly collected and stored in a special glass container (with a capacity of 20 needles) and then sent to the sterile department of each hospital for autoclave sterilization. An exclusive supervisor at each center will take charge of monitoring this procedure to ensure that only the silver needles with qualified disinfection can be reused. For the control group, the needles are disposable, stainless steel filiform needles (Jiajian Medical Material Co., Ltd., Wuxi, China) and will be applied for single use.

### Outcome measures

The assessments consist of two self-assessment instruments and a physician-based questionnaire (all Chinese versions) in addition to a routine medical history review and physical examination. Assessments will be performed before allocation at screening (T0, baseline), a week after the final treatment (T1, primary endpoint), 13 weeks after the final treatment (T2, secondary endpoint), and 25 weeks after the final treatment (T3, final endpoint). The timeframe of data collection and assessments is shown in Fig. 2 (the SPIRIT figure).

**Fig. 2 Fig2:**
[figure not shown]
SPIRIT figure: schedule of enrollment, allocation, intervention, and assessments. *TCM* traditional Chinese medicine, *Qol* quality of life, *ODI* Oswestry Disability Index, *VAS* visual analog scale, *JOABPEQ* Japanese Orthopedic Association Back Pain Evaluation Questionnaire, *CEQ* credibility/expectancy questionnaire

#### Primary outcome measure

The primary outcome measure is the change in the ODI. The ODI involves 10 questions which mainly evaluate pain severity, self-sufficiency level, and quality of daily life [14]. Each question is calculated from 0 to 5 and then added up into an overall score. The higher the overall score is, the worse the general condition.

#### Secondary outcome measures

Secondary outcome measures include the following:In order to determine the improvement of pain intensity more precisely, the visual analog scale (VAS) from 0 to 100 will be chosen as one of the secondary outcome assessment tools.The Japanese Orthopedic Association Back Pain Evaluation Questionnaire (JOABPEQ) is a commonly used index in evaluating the treatment effect of LDH [15]. Considering its overlaps of the measurement of pain-related disorders, gait disturbance, social life disturbance, and psychological dysfunction with the ODI, we selectively assess three items in JOABPEQ which only evaluate the lumbar spine dysfunction.

In addition to these assessments, participants will also be required to complete an extra six-item-scale questionnaire [16] immediately after the first treatment, so that we can explore whether or not there is a significant difference in treatment expectancy and rationale credibility between the two groups.

#### Adverse events reporting and safety monitoring

Through the written informed consent form and detailed explanations, we ensure that every participant is aware of common adverse events related to acupuncture or warm needling treatment (such as bruising at the local area, sustained soreness or numbness, feeling faint, blistering due to overheating) as well as serious adverse events (classified as life-threatening, permanently incapacitating, or requiring hospitalization). During the treatment, participants must report any adverse events they experience to the project acupuncturists, while the latter must also record adverse events they themselves observe. All adverse events will be collected and presented promptly in detail to the assessors, who will decide on subsequent management (including intimate observation, additional medical management, or an early closure of participation) and record both the adverse events and the final outcome in the CRF.

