### Statistical methods

In accordance with the intention-to-treat (ITT) principle, incomplete data will be collected, and reasons for missing data should be presented clearly so that the statistician can handle missing data with the appropriate statistical approach.

In general, all original data extracted from our online custom-designed database will be analyzed with SPSS Statistics version 22.0 software by a statistician. Continuous variables with a normal distribution will be expressed in the form of mean ± standard deviation, while continuous variables with a non-normal distribution or ordinal variables in the form of medians (with lower and upper quartiles), and categorical variables will be described as counts and proportions. To detect the statistically significant difference between the two groups, the independent sample *t* test will be performed for measurement data, the χ^2^ test for categorical data, and the Mann-Whitney *U* test for data that conform to an abnormal distribution. Any reported *p* value (two-sided) less than 0.05, with 95% confidence intervals, will be interpreted as the indication of a statistically significant difference.

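### The protocol lets an adverse event end participation without saying whether outcome assessment continues, which leaves the intention-to-treat claim unsecured for the primary ODI outcome

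*Protocol article*

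**What the plan says.** The section on adverse events and safety monitoring has events reported to the assessors, who decide what follows. The options are given as "including intimate observation, additional medical management, or an early closure of participation". The section does not say whether a patient whose participation is closed still completes the questionnaires.

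The Statistical methods section begins "In accordance with the intention-to-treat (ITT) principle, incomplete data will be collected". It asks for the reasons for missing data "so that the statistician can handle missing data with the appropriate statistical approach". For between-group differences it names the independent-samples t test, the chi-squared test and the Mann-Whitney test.

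The Outcome measures section lists four assessments: T0 before allocation, T1 (the primary endpoint) one week after the last session, then T2 and T3 at 13 and 25 weeks after it. The primary outcome is the change in ODI. Treatment runs for nine sessions over three weeks.

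The Sample size section states "Allowing for a sample loss of 20%, the final sample size is inflated to 160 in total".

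**The concern.** Intention-to-treat requires that an outcome be sought from everyone randomized, whether or not they stay on treatment. A rule that closes participation, read plainly, ends both. The schedule makes this matter. Adverse events are to be reported during treatment, and the listed schedule has no ODI in that period. A patient closed out then has a baseline score only, so no change in ODI exists at T1 or later.

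This is a rule of conduct, not an analysis detail. A statistical analysis plan can choose how to handle missing values, but it cannot recover questionnaires that were never requested.

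Whether such loss could differ by arm is a fair question on the protocol's own rationale. Needle material is the only planned difference between arms, the Discussion cites roughly sevenfold heat transfer for silver, and blisters from overheating are among the listed events. If loss differs by arm and the missing patients fare differently from those observed, the observed difference is shifted. Recruiting more patients does not remove that shift.

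**Working it through.** **1. The plan's own sample size.**
- Inputs, from the Sample size section: the cited trial's ODI "decreased to 26.29 ± 18.02 in the intervention group" and "34.58 ± 15.10 in the control group", two-sided alpha 0.05, power 80%.
- Difference = 34.58 − 26.29 = 8.29.
- Pooled SD = √[(18.02² + 15.10²)/2] = 16.62. Standardised difference = 8.29/16.62 = 0.499.
- n per arm = 2 × (1.960 + 0.842)² × 16.62²/8.29², which rounds up to 64, or 128 in total. The t-based solution is 64.1 per arm.
- Inflation: 128/(1 − 0.20) = 160. Both stated figures reproduce.

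**2. What the inflation achieves.** With 64 per arm observed, power is 80.5% (normal approximation) or 79.9% (t). With all 80 per arm observed it is 88.4% or 88.0%. The allowance therefore does its job for power. It has no bearing on bias.

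**3. Shift from unequal loss (illustration only).** Let d_A and d_B be the proportions lost on silver and steel, and let missing patients be k ODI points worse than observed ones in both arms, on the scale of the cited means. Each arm's full mean is its observed mean plus d × k. A comparison of observed values is therefore shifted by (d_A − d_B) × k. The losses and k are assumptions. In every case below the total lost is 32 of 160, the plan's 20%.

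| Loss, silver / steel | Patients lost | k = 5 | k = 10 | k = 20 |
|---|---|---|---|---|
| 20% / 20% | 16 / 16 | 0 | 0 | 0 |
| 25% / 15% | 20 / 12 | 0.5 | 1.0 | 2.0 |
| 30% / 10% | 24 / 8 | 1.0 | 2.0 | 4.0 |

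At k = 10 the shifts are 1.0/8.29 = 12% and 2.0/8.29 = 24% of the planned difference. Exchanging the arms reverses the sign.

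**4. Effect on false positives.** If there were no true difference, the standard error would be 16.62 × √(1/n_A + 1/n_B).
- At 25%/15%, n = 60 and 68. Two-sided type I error is 5.3% at k = 5, 6.3% at k = 10 and 10.4% at k = 20.
- At 30%/10%, n = 56 and 72. It is 6.3%, 10.4% and 27.2%.
- At equal loss it stays at 5.0%.

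**5. Scale per patient.** With 80 randomized per arm and k = 10, each net extra loss in one arm moves the difference by 10/80 = 0.125 points. The 1.0 and 2.0 point shifts need net excesses of 8 and 16 patients from all causes together. A few adverse-event closures alone would move it far less.

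**The case against.** The best defence is that the protocol commits to intention-to-treat, to collecting incomplete data and to handling missing values, and nowhere excludes non-completers. Ending participation is one of three management options, and continued assessment is not ruled out. The named missing-data method properly belongs in an analysis plan that is not shown, and the outcome statistician is blinded. All of this stands, and the missing method is not counted against the plan here.

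A reader might go further and infer four things that the documents do not support:
- That the plan is a completer analysis as written. The Statistical methods section says otherwise, and a t test can be run after missing values have been handled.
- That lost patients are replaced. The number is inflated in advance, and no section provides for replacement.
- That each visit is tested separately. The section does not say so, and T1 is the primary endpoint.
- That the bias must favour silver. No adverse-event or loss rate is given by arm. The Background, Treatment regimen and Discussion sections expect temperature control to limit burns. Dropout for lack of effect on steel would push the other way, and a blister need not mean a worse ODI.

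The defence does not answer the conduct rule. Collecting incomplete data does not say that a patient whose participation has been closed is still assessed, and the listed schedule offers no earlier ODI to fall back on.

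**Conclusion.** The point holds in a limited form. The adverse-event section and the intention-to-treat statement need to be reconciled, because on its plain reading the former can leave a randomized patient with no primary outcome. The 20% allowance is correct and protects power only.

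The size is not known. Under assumed 25%/15% to 30%/10% loss, with missing patients 5 to 20 points worse, the shift runs from 0.5 to 4.0 points. It is zero if loss and deficit are the same in both arms. These figures rest on invented loss rates and outcome gaps, cover loss from all causes, and do not establish a direction. The schedule figure is not available, so the statement about T0 and T1 rests on the text of the Outcome measures section.

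The unadjusted t test is a lesser matter. Adjusting for baseline ODI would be expected to improve precision, but no model gains much from a patient with no post-baseline score. Continued assessment is therefore the main remedy.

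**What to change.** - **Conduct.** State in the adverse-event section that, whatever is decided about treatment, T1 to T3 questionnaires are still sought, by telephone if needed, unless the patient withdraws consent. This leaves the clinical decision untouched.
- **Analysis set.** State that all randomized patients are analysed in their allocated arm.
- **Primary analysis.** Replace the unadjusted two-sample t test on ODI with a baseline-adjusted analysis. One example is a mixed model for T1 to T3 with baseline ODI, centre and arm by visit, with the T1 contrast as primary.
- **Sensitivity analysis.** Shift missing ODI values over a stated range in either arm and in both, so that no direction is built in.

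The cost is a few sentences, some telephone calls and slightly more analysis. The sample size of 160 does not change. If the full protocol already requires continued assessment, only the wording of the adverse-event section needs to be aligned with it.
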